## 12.6 List of Changes from Protocol Version 6.0 to Version 8.0

The changes that were made to protocol version 6.0 (dated 18 May 2010) to create version 8.0 of the protocol are described below. Note that version 7.0 of the protocol was reviewed internally but was neither submitted for regulatory review nor implemented by the clinical site.

| Section Number (Title)                                          | Version 6.0                                                                                                                                                                                                                                                                                                                                                                        | Version 8.0                                                                                                                                                                                                                                                                                    |
|-----------------------------------------------------------------|------------------------------------------------------------------------------------------------------------------------------------------------------------------------------------------------------------------------------------------------------------------------------------------------------------------------------------------------------------------------------------|------------------------------------------------------------------------------------------------------------------------------------------------------------------------------------------------------------------------------------------------------------------------------------------------|
| Study Abstract and Section 2.2 (“Study Design”)          | Change/rationale: As described in the protocol (Section 7.6, Sample Size Considerations), an independent statistician performed a sample size review using an interim pooled estimate of the TB event rate. Based on this analysis, it was determined that an additional 6 months of follow-up were required to maintain sufficient power to detect a 60% vaccine efficacy. |                                                                                                                                                                                                                                                                                                |
|                                                                 | Given completion of enrollment in 21 months, all infants will be followed for at least 9 months after the last infant is enrolled into the study. The total duration of follow-up for each infant is at least 9 months and up to 33 months, with additional follow-up time to be determined based on sample size review.                                                           | Given completion of enrollment in 21 months, all infants will be followed for at least 15 months after the last infant is enrolled into the study. The total duration of follow-up for each infant is at least 15 months and up to 39 months.                                                  |
| Section 3.1, (“Summary Schedule of Subject Evaluations”) | Change/rationale: Follow-up was extended as discussed above.                                                                                                                                                                                                                                                                                                                |                                                                                                                                                                                                                                                                                                |
|                                                                 | Follow up of all infants will be terminated at the next scheduled study visit after the last enrollee completes 9 months of follow-up (Study Day 252).                                                                                                                                                                                                                             | Follow up of all infants will be terminated at the next scheduled study visit after the last enrollee completes 15 months of follow-up (Study Day 420).                                                                                                                                        |
| Section 7.6, (“Sample Size Considerations”)              | Change/rationale: Follow-up was extended as discussed above.                                                                                                                                                                                                                                                                                                                |                                                                                                                                                                                                                                                                                                |
|                                                                 | Calculations assume 90% power to detect a 60% reduction in tuberculosis rate between the MVA85A/AERAS-485 and control groups; given an estimated enrollment over 21 months, the last subject to enroll in the study will be followed for a minimum of 9 months to maintain statistical power.                                                                                      | Calculations assume 90% power to detect a 60% reduction in tuberculosis rate between the MVA85A/AERAS-485 and control groups; given an estimated enrollment over 21 months, the last subject to enroll in the study will be followed for a minimum of 15 months to maintain statistical power. |
| Throughout                                               | Change/rationale: The name "Aeras Global TB Vaccine Foundation" was changed to "Aeras" to reflect the sponsor's new name.                                                                                                                                                                                                                                                   |                                                                                                                                                                                                                                                                                                |

## Appendix A: Subject Diary

|                            |                                               |
|----------------------------|-----------------------------------------------|
| C-020-485
TB020 | Subject Number
 |
|----------------------------|-----------------------------------------------|

**Office: [name] (between 0800 & 1600)**

***Out of hours: [name]***

Subject Number

If there is nothing to record write "0" *do not leave blank.*

|                   |             |             |                            | Have these happened since the last time you recorded your baby's observations? |                        | Measurement (mm) |          |
|-------------------|-------------|-------------|----------------------------|--------------------------------------------------------------------------------|------------------------|------------------|----------|
| Day after Vaccine | Date        | Time (24hr) | Temperature in armpit (°C) | Pain
(circle maximum score)                                                 | Warmth
(0=No 1=Yes) | Redness          | Swelling |
| 0                 | DD/MMM/YYYY |             |                            | 0 1 2                                                                          |                        |                  |          |
| 1                 | DD/MMM/YYYY |             |                            | 0 1 2                                                                          |                        |                  |          |
| 2                 | DD/MMM/YYYY |             |                            | 0 1 2                                                                          |                        |                  |          |
| 3                 | DD/MMM/YYYY |             |                            | 0 1 2                                                                          |                        |                  |          |
| 4                 | DD/MMM/YYYY |             |                            | 0 1 2                                                                          |                        |                  |          |
| 5                 | DD/MMM/YYYY |             |                            | 0 1 2                                                                          |                        |                  |          |
| 6                 | DD/MMM/YYYY |             |                            | 0 1 2                                                                          |                        |                  |          |
| 7                 | DD/MMM/YYYY |             |                            | 0 1 2                                                                          |                        |                  |          |

**Pain Score**

0= Baby seems unaware of injection site  
1= Baby cries when injection site is touched  
2= Baby cries when arm is moved

**Warmth**

Is the injection site on your baby's arm warm?  
0= No  
1= Yes

**Pain Score**

Use the tape measure provided to measure ANY redness (bright pink) or swelling, and try to record everything at approximately the same time each evening.  
Measure the diameter (size) of redness and swelling by putting the tape measure through the actual vaccine site.  
Record all signs your baby has experienced since the last time you recorded them up to and including the time you take the measurements.

[figure not shown]

Subject Number

| Day | Date     | Feeds less than usual | Sleeps less than usual | Sleeps more than usual | Less alert (awake) than usual | Feverish | Irritable (bad tempered) | Diarrhoea (number of times today) | Vomiting (number of times today) |
|-----|----------|-----------------------|------------------------|------------------------|-------------------------------|----------|--------------------------|-----------------------------------|----------------------------------|
| 0   | DD/MM/YY |                       |                        |                        |                               |          |                          |                                   |                                  |
| 1   | DD/MM/YY |                       |                        |                        |                               |          |                          |                                   |                                  |
| 2   | DD/MM/YY |                       |                        |                        |                               |          |                          |                                   |                                  |
| 3   | DD/MM/YY |                       |                        |                        |                               |          |                          |                                   |                                  |
| 4   | DD/MM/YY |                       |                        |                        |                               |          |                          |                                   |                                  |
| 5   | DD/MM/YY |                       |                        |                        |                               |          |                          |                                   |                                  |
| 6   | DD/MM/YY |                       |                        |                        |                               |          |                          |                                   |                                  |
| 7   | DD/MM/YY |                       |                        |                        |                               |          |                          |                                   |                                  |

*Please indicate if your baby has experienced any of these symptoms since the last time you recorded their symptoms.  
Write 'Yes' or 'No' and, if Yes, please also write the number of times.*

Subject Number

| Other problems | Start date  | Stop date   | Medications taken
(include dose (amount) and how often your baby took them) |
|----------------|-------------|-------------|--------------------------------------------------------------------------------|
|                | DD/MMM/YYYY | DD/MMM/YYYY |                                                                                |
|                | DD/MMM/YYYY | DD/MMM/YYYY |                                                                                |
|                | DD/MMM/YYYY | DD/MMM/YYYY |                                                                                |
|                | DD/MMM/YYYY | DD/MMM/YYYY |                                                                                |
|                | DD/MMM/YYYY | DD/MMM/YYYY |                                                                                |
|                | DD/MMM/YYYY | DD/MMM/YYYY |                                                                                |
|                | DD/MMM/YYYY | DD/MMM/YYYY |                                                                                |
|                | DD/MMM/YYYY | DD/MMM/YYYY |                                                                                |
|                | DD/MMM/YYYY | DD/MMM/YYYY |                                                                                |
|                | DD/MMM/YYYY | DD/MMM/YYYY |                                                                                |
|                | DD/MMM/YYYY | DD/MMM/YYYY |                                                                                |

Please use this table to describe any other symptoms your baby has experienced, even if you do not think they are anything to do with the vaccine, and record any medications your baby takes (remedies, herbal preparations, creams, ointments etc).

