### 5.3 Definition of Adverse Event

An adverse event (AE) is defined as any unanticipated problem involving risks to study participants or others. An adverse event, therefore, can be any unfavorable or unintended sign, symptom, disease, syndrome, abnormal laboratory finding, or concurrent illness that

emerges or worsens relative to the infant's pretreatment baseline, whether or not it is considered to be related to the medicinal product.

All conditions that exist prior to administration of the study vaccine (pre-existing conditions) will be recorded in the infant's medical history to establish baseline. Day-to-day fluctuations in pre-existing conditions that do not represent a clinically significant change in the infant's status will not necessarily be reported as adverse events.

Any adverse change from the infant's baseline condition (determined from screening evaluations conducted to confirm study eligibility) that occurs following the administration of the study vaccine will be considered an adverse event. This includes the occurrence of a new adverse event or the worsening of a baseline condition, whether or not considered related to the study vaccine. Intermittent conditions such as headaches may be present on Study Day 0 but may represent an adverse event if the intensity or duration of the event is worse than usual following receipt of study vaccine. Adverse events include but are not limited to: adverse changes from baseline that represent increases in toxicity grade according to the Toxicity Table (see protocol appendices), adverse changes in the general condition of the infant, signs and symptoms noted by the infant's caregiver, concomitant disease with onset or increased severity after study vaccine administration, and changes in laboratory safety parameters occurring after study vaccine administration.

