| Systemic (General)                 | Grade 1                                                           | Grade 2                                                            | Grade 3                                                              | Grade 4 |
|------------------------------------|-------------------------------------------------------------------|--------------------------------------------------------------------|----------------------------------------------------------------------|---------|
| Decreased oral intake              | Minimal decrease in oral intake                                   | Below 50% of normal oral intake in 24 hr                           | No oral intake in 24hr                                               | N/A     |
| Vomiting                           | 1 episode in 24hr; no interference with activity                  | 2-3 episodes in 24 hr OR some interference with activity           | > 3 episodes in 24 hours OR prevents daily activity                  | N/A     |
| Diarrhea                           | Unformed stool OR 1-3 more stools than baseline in 24 hr          | Partially liquid stools OR 4-6 more stools than baseline in 24hr   | Completely liquid stools OR >6 more stools than baseline in 24 hr    | N/A     |
| Irritability                       | Easily consolable; minimal or no interference with activity       | Difficult to console; some interference with activity              | Inconsolable; prevents daily activity                                | N/A     |
| Fatigue                            | Minimal or no interference with activity                          | Some interference with activity                                    | Prevents daily activity                                              | N/A     |
| Lethargy                           | Minimal decrease in alertness; minimal interference with activity | Some interference with activity                                    | Unable to achieve normal level of alertness; prevents daily activity | N/A     |
| Illness or clinical adverse event) | Minimal or no interference with activity                          | Some interference with activity not requiring medical intervention | Prevents daily activity and requires medical intervention            | N/A     |

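### The diary's vomiting and diarrhoea columns carry two conflicting counting windows, and neither starts Day 0 at the injection, so some counts and grades can be wrong by an unknown amount

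*Protocol*

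**What the plan says.** The second grid of the diary in Appendix A has one row per day, Day 0 to Day 7. Its two count columns are headed "Diarrhoea (number of times today" and "Vomiting (number of times today". The instruction beneath the same grid reads "Please indicate if your baby has experienced any of these symptoms since the last time you recorded their symptoms", and continues: "Write 'Yes' or 'No' and, if Yes, please also write the number of times". The count, and not only the yes/no answer, is therefore tied to the previous entry.

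The local-reaction page sets the time of entry: "try to record everything at approximately the same time each evening". That page uses a single window: "Record all signs your baby has experienced since the last time you recorded them up to and including the time you take the measurements".

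Appendix C grades vomiting by episodes in 24 hours. Grade 2, for example, is "2-3 episodes in 24 hr OR some interference with activity". Diarrhoea is graded by stool consistency or by stools above baseline in 24 hours. Section 5.3 says that an adverse change from baseline that "occurs following the administration of the study vaccine will be considered an adverse event".

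Section 5.7 names diarrhoea and vomiting as solicited events and makes the diary their source document. Section 7.5.1 places solicited events in the primary safety variable and summarises them by severity, counting each subject once per term at the worst grade.

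**The concern.** Two parents can see the same day of vomiting and write different numbers, each following an instruction printed on the page. With an evening entry, 'today' means midnight to the time of writing, and the hours from then to midnight fall in no row. Counting from the previous entry loses no hours and gives rows of about 24 hours, which is the unit of Appendix C.

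Day 0 fits neither wording. 'Today' includes the morning before the injection. 'Since the last time' has no earlier entry to count from.

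The systemic grid has no time column, so a reviewer cannot see which window the parent used or whether a Day 0 episode came before the injection. Safety is the primary objective and the analysis is descriptive, so absolute rates and grades are themselves the result.

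**Working it through.** The plan states no figure that depends on the diary window, so there is none to reproduce. The contradiction is established by reading. The arithmetic below only shows how far the windows can diverge.

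**Windows side by side**

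| Row | Heading ('today') | Instruction (since last entry) | Appendix C / Section 5.3 |
|---|---|---|---|
| Day 0 | Midnight to entry; includes hours before the injection | No earlier entry to count from | Only what follows the injection |
| Days 1–7 | Midnight to entry; under 24 h | Entry to entry; about 24 h | 24 h |

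**Assumptions (not in the documents).** Entry at 18:00 to 22:00, injection at 08:00 to 15:00, episodes spread evenly over 24 hours.

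**1. Hours in no row under a literal 'today'.** This is 24 − entry hour.
- 18:00: 6 h, 6/24 = 25%.
- 20:00: 4 h, 4/24 = 17%.
- 22:00: 2 h, 2/24 = 8%.

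Under the instruction it is 0 h.

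**2. Days 1–7, vomiting graded on count alone.** Let w = entry hour/24, so w runs from 0.75 (18:00) to 22/24 = 0.917 (22:00).
- One episode is missed with probability 1 − w = 0.08 to 0.25.
- Two episodes (Grade 2) fall below Grade 2 with probability 1 − w² = 0.16 to 0.44.
- Four episodes (Grade 3) fall below Grade 3 with probability 1 − w⁴ = 0.29 to 0.68.

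**3. The same loss with a random number of episodes.** Take the daily number as Poisson and keep each episode with probability w. The table gives the probability that the row's grade is lowered, given at least one episode:

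| Mean episodes per day | Entry 18:00 | Entry 20:00 | Entry 22:00 |
|---|---|---|---|
| 1 | 0.306 | 0.207 | 0.104 |
| 2 | 0.337 | 0.226 | 0.113 |
| 4 | 0.333 | 0.215 | 0.103 |

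That is about 10 to 34% of days with any vomiting, and only for parents who follow the heading literally.

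**4. Day 0.** The share of the 'today' window before the injection is injection hour/entry hour. It runs from 8/22 = 36% to 15/18 = 83%; a 10:00 injection with a 20:00 entry gives 50%. These are shares of clock hours, not of events.

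**5. A limit of any once-daily count.** Suppose vomiting occurs at 07:00, 12:00, 18:00 and 22:00 on one day, with entry at 20:00. Both wordings put 3 in that day's row (Grade 2), although four episodes fell within 24 hours (Grade 3). Under the heading the 22:00 episode disappears. Under the instruction it appears in the next row, where a reviewer can see it.

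**The case against.** The best defence is that the full instruction governs. It covers the count explicitly and matches the local-reaction page. A parent who follows it loses nothing and produces rows of about 24 hours.

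Several other provisions also limit the damage:
- Section 5.15 gives the diary to parents of vaccinated infants, has them instructed in its use after administration, and has the investigator review it and obtain missing details. Pre-injection episodes are not adverse events under Section 5.3 and can be removed at that review.
- Section 3.2.3.2 excludes acute illness, fever and significant active infection on Day 0, so pre-injection episodes should be few.
- Appendix C is not graded on counts alone. Interference with activity, or stool consistency, can hold a grade up.
- Only the worst grade per subject and term is summarised, so an undercount on one day often changes nothing.

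All of this stands as a limit on size. It does not remove the contradiction. Review takes place at a scheduled visit, the first at Day 7 (±2 days), and the grid records no times, so correction rests on the parent's memory.

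A reader might go further and infer that grades on Days 1 to 7 are understated, that Day 0 rates contain pre-vaccination events, and that both errors dilute the comparison between arms. The documents do not support this. The first holds only where parents follow the heading literally, and nothing shows how many would. The second requires such episodes to occur and to survive review. On the third, both arms use the same diary under blinding. If each arm detects the same fraction s of affected subjects, with no false positives, the risk ratio s·p₁/(s·p₀) is unchanged and only the difference s·(p₁ − p₀) shrinks. Retained pre-injection episodes could pull the ratio toward 1, but there should be few.

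One page of the diary ahead of the first grid was not available here. Any instruction on it could not be checked, though the heading and the instruction would still conflict.

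**Conclusion.** The point holds as a contradiction on the diary page. The same two counts have two windows that differ every day, and neither is anchored to the injection on Day 0. Counts can therefore differ between parents, some grades can be understated against Appendix C, and Day 0 can include episodes outside the adverse-event definition.

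The size is unknown. The percentages above depend on assumed entry and injection times, evenly spread episodes, literal use of the heading and grading on count alone. They describe single diary rows, not the reported worst grade per subject. The main exposure is in absolute counts and grades; the error should be similar in both arms, and no bias favouring either arm is shown. It is more than clerical because the diary is the source for solicited events in the primary safety variable, and the window a parent used cannot be recovered from the page.

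**What to change.** In the second grid of Appendix A:
- Change both count headings to 'number of times since you last filled in the diary', so that they agree with the instruction below.
- Have the Day 0 row read 'since the injection'.
- Apply the 24-hour counts of Appendix C to the Day 1 to Day 7 rows.
- Treat Day 0 as a partial-day count. On the assumed times it covers 3 h (15:00 injection, 18:00 entry) to 14 h (08:00 injection, 22:00 entry), so it cannot stand as a full 24-hour count.

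No post-injection hour up to the last entry is then uncovered and no pre-injection hour is counted. The cost is a wording change in the diary and a line in the grading conventions, with no added visit or procedure. Diaries already completed under the present wording cannot be repaired this way; for those, the report should state the ambiguity and show Day 0 separately.
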